#### HEALD-PCN intervention

The HEALD-PCN intervention is based on a previously pilot-tested self-management program in this patient population [23]. It consists of two phases, lasting a total of 24 weeks, with emphasis on physical activity (walking) and nutritional elements. During weeks 1 to 12 (phase 1), participants allocated to the intervention group will be placed in a self-monitored, pedometer-based walking program targeting total daily steps. With initial guidance from an Exercise Specialist, each participant will set his or her own daily step goals. A baseline average will be calculated from three consecutive days including one weekend day [23-25] to help participants set individualized goals. The program goal for all participants over the first 12 weeks (phase 1) will be to increase their number of steps/day.

As part of phase 1, during weeks 1 and 2, participants will attend a 30-minute, group-based meeting, including a supervised walking session, facilitated by the Exercise Specialist, and located at a community recreation facility. A pedometer, a resource manual and step logbook will be provided at the first meeting to facilitate goal setting and to record the total number of steps/day. Access to the community recreation facility is based on partnership arrangements between the research team, the PCN and the local recreation facility management. Financial arrangements for these agreements are provided by the research funding. After week 12 (phase 2), participants will be asked to continue to walk the same number of steps/day that they walked during weeks 10-12 of phase 1. As part of phase 2, during weeks 13 and 14 participants will attend two more group-based meetings at the same community recreation facility, where they will be taught by the PCN Exercise Specialist how to increase their walking speed by 10% during a 30 minute walk. The participants will be asked to incorporate this faster walking pace for 30 minutes/day on 3 days/week on their own, until the end of the study period. For example, if a participants’ self-selected walking pace was 90 steps/minute, they will be encouraged to increase his or hers’ pace to approximately 100 steps/minute. Participants will be asked to perform their faster walking in bouts lasting no less than 10 minutes, and will be given a second pedometer and a stopwatch to help them measure and monitor their brisk steps and time. A second resource manual will be given to accompany this part of the program, which will include a set of small portable cards to record the number of brisk steps immediately after they are performed.

The nutritional element of the HEALD-PCN program will focus on the concepts of the Glycemic Index (GI) in accordance with the Canadian Diabetes Association Clinical Practice Guidelines [2]. The goal will be to increase daily consumption of low-GI foods. Participants will be encouraged to exchange high-GI foods with low-GI foods (i.e. replace white or whole wheat bread with pumpernickel) on at least 3 days/week and to make at least 2 exchanges over the course of those days. Glycemic index goals will be based on the Good-Better-Best principle proposed by Brand-Miller and Foster-Powell [26] which suggests a “this-for-that” exchange system whereby low-GI foods are euphemistically termed leakers (i.e., the “this”) should replace high glycemic index foods termed gushers (i.e., the “that”) in the diet. Achieving high task self- efficacy for identifying low and high glycemic index foods is considered an essential component of this study. We have previously shown this approach increases general GI knowledge [27].

#### Program delivery training for exercise specialists

One Exercise Specialist (i.e., certified by the Canadian Society of Exercise Physiology) will administer the intervention at each PCN. A full day workshop for all specialist detailing the delivery of the HEALD intervention will be organized and led by [name] (developer of the HEALD intervention). [name] will also meet with each Exercise Specialist at each PCN to review the HEALD materials prior to the delivery of the first HEALD group session. Study manuals that cover all aspects of the HEALD intervention will be provided at the training workshop.

#### Usual care

Participants in the usual care or “Off” group will receive usual or standard care for diabetes from their family physicians and/or chronic disease management team based on clinical practice guidelines. Participants in this group will be followed up for the same time (i.e., 6 months) and will undergo all the assessments and measurements as participants in the intervention group.

#### Study measures

We will use a combination of metrics to determine the effectiveness of the HEALD-PCN. As in our HEALD pilot study [23], the primary outcome is physical activity determined by self- report and pedometers. Secondary outcomes include nutrition behaviours (healthy eating and glycemic index), anthropometric assessments, and biomarkers. All primary and secondary outcomes will be collected at baseline, 3 and 6 months, through surveys and point of care instrument testing. Demographic, health/medical and other related characteristics will also be assessed at baseline, 3 and 6 months. At study completion, we will assess self-reported health status and satisfaction with the intervention materials and pedometers. We will also collect information on the cost of this enhanced lifestyle program in the PCN environment and subsequent participant health care utilization, through linkages with Alberta administrative data. To do so, participants enrolled in the study will be asked for permission to access their medical records by signing a consent form and providing their personal health number, thus allowing linkage to Alberta Health and Wellness physician billing, hospital billing, and emergency room billing data. This linkage will allow health care utilization and health care costs to be included in the evaluation.

##### Physical activity behaviours

Our primary outcome is self-reported physical activity, assessed with the Godin Leisure Time Exercise Questionnaire (GLTEQ) [28], modified to calculate MET minutes values [29] for total moderate and vigorous physical activity. The GLTEQ asks participants to report the average number of times per week, in the past month, they engaged in vigorous (rapid heartbeats, sweating), moderate (not exhausting, light perspiration) and mild (minimal effort and no perspiration) intensity PA, for a minimum of 10 minutes per session. Participant responses for the moderate and vigorous activity categories will be added together to calculate moderate and vigorous physical activity (MVPA) minutes per week and will serve as our primary self-report outcome measure.

For walking specific behaviors, pedometers (Yamax SW-200) and step logs will also serve as an objective measure of our primary outcome. Participants in both the intervention and control groups will be provided with a pedometer, and instructed to wear it and record total daily step-counts in a log for 3 consecutive days including one weekend day. The step log also allows for the collection of brisk steps for the intervention group. Self-reported walking will also be assessed using questions form the International Physical Activity Questionnaire (IPAQ) long version [30]. Participants will be asked, “During the last 7 days on how many days did you walk for at least 10 minutes at a time to go from place to place” or “in your leisure time”. Participants will then be asked, “How much time did you usually spend on ONE of those days walking from place to place” or “walking in your leisure time”. Responses will be recorded in days, hours, and/or minutes per day. A walking score will be calculated by multiplying the number of walking days by the walking minutes then by 3.3 (the MET value suggested for walking) to obtain walking scores in MET-minutes. Stages of physical activity behaviour change measures (≥ moderate levels) initially developed by Reed and colleagues [31] will serve as a secondary behavioral outcome (to assess stage transition).

##### Clinical measures

Using previously validated point of care testing devices, participants will have fasting capillary blood samples collected to assess hemoglobin A1c (DCA Vantage), lipid profile, glucose (Cholestech LDX), resting heart rate and blood pressure (BPTru). These clinical measures will be taken at baseline, 3 and 6 months. Anthropometric measurements including weight, height, and waist and hip circumference will be completed and body mass index (BMI) calculated.

##### Other measures

For nutrition behaviours, a validated food frequency questionnaire [32] will be used to estimate saturated fat, trans fat, total sugars, "added sugars" (in sweetened cereals, soft drinks, and sweets), fruit and fruit juice, vegetable intake, glycemic load and glycemic index. Validated published measures of health related quality of life [33-35], depressive symptoms using the Patient Health Questionnaire-9 [36-38], problem areas in diabetes [39], medication use, foot care, smoking behaviour, history of chronic diseases and risk factors [40]. Social cognitive variables related to physical activity behaviors from protection motivation theory, theory of planned behaviour, social cognitive theory, and stages of change will also be examined at baseline, 3 and 6 months using validated measures [41].

##### Implementation evaluation

By applying the RE-AIM Framework, our academic group and PCN partners are highly engaged in facilitating an in-depth understanding of the process variables necessary to inform the successful future adoption and sustainability of this intervention in similar primary care settings. The RE-AIM framework provides a systematic means to evaluate the overall population-based impact of an intervention and it’s potential for translation through five components that describe: Reach, Effectiveness, Adoption, Implementation, and Maintenance [42].

Unlike studies focused only on efficacy, the RE-AIM framework emphasizes both internal and external validity while considering both individual and system level outcomes [41]. It serves to prioritize public health issues as it impacts real world settings, facilitating the translation of research into practice [42]. This framework has been applied in the evaluation of several health behaviour change interventions, specifically those that target physical activity, and diabetes [42-45]. The RE-AIM framework has been incorporated into the HEALD implementation and evaluation framework, through the use of a logic model and data matrix, that outlines evaluation questions, indicators and metrics, and data sources.

Our proposed evaluation activities that will inform dimensions of RE-AIM include systematic documentation of (a) usual care related to lifestyle counseling, (b) PCN organizational factors and strategies, (c) readiness and ability to implement HEALD through a checklist and interview guide administered to the Executive Directors, Chronic Disease Managers at each PCN, and (d) implementation facilitators and barriers identified by the Exercise Specialists. Data collected through the RE-AIM framework serves several evaluative functions: 1) determining the overall public health impact and translatability/applicability, 2) comparing the intervention’s public health impact across settings overtime, 3) comparing interventions across the various RE-AIM components, 4) assisting in the decision-making process of resource allocation for more effective programs, 5) providing information related to the level of implementation across the stages of research, and (6) providing valuable information to PCNs on the sustainability of long-term behaviour change (at patient and organization/system levels) beyond the intervention. All of these purposes have been highlighted in the diabetes literature as essential components to progress the research base in behaviour change [42,45-47].

##### Qualitative follow-up

To enhance to the validity of the quantitative findings and provide further information on the natural history (albeit retrospective) of the adoption of positive health behaviours for self-management, 10% of the participants (from each of the study groups at each of the PCNs) will be randomly selected to participate in a structured qualitative telephone interview at 6 months following the completion of the HEALD intervention. We hope to explicate their attitudes and behaviours related to the process of their healthy eating and active living behaviour change (or lack there of) and the program components.

### Analytic strategy

All statistical tests will be two-sided with a level of significance set at 0.05 to evaluate the effectiveness of the intervention. Baseline comparisons will be performed using univariate analysis of variance (ANOVA) for continuous variables and chi-square analyses for categorical variables. The main analysis of our study is to compare the physical activity of the HEALD-PCN intervention (On) group participants to the usual care (Off) group, from baseline to 6 months as our primary assessment time-point. Employing the intention-to-treat (ITT) approach, we will also assess differences in group changes from: (1) baseline to 3 months, (2) baseline to 6 months, (3) and 3 months to 6 months using generalized linear mixed-model analysis (GLMM). GLMM uses all available data and provide a valid analysis when data are missing at random. The models will use baseline values for each outcome variable as a covariate to reduce the residual standard error and account for regression to the mean. Potential confounding variables (i.e., age, sex and BMI) will be included as covariates in the models. All data will be analyzed using Statistical Package for the Social Sciences v.20, SPSS Inc., Chicago Illinois, USA and Stata SE 10.1, StatCorp, College Station, Texas, USA.

Based on the study’s design, we will account for 2 measurement points for the main dependent outcome (i.e., physical activity behavior at 6 months) across the study groups. In a 2 time-point, 2 group, repeated measures design with an a priori fixed and random effects model set to detect a moderate effect size (f = 0.25) while assuming a modest correlation (r = 0.5), the required sample size is 86 participants per group (power = 0.90; alpha = 0.05) [48-50]. Sample size was also estimated at 75 participants per group for average steps per day assuming an increase of 1,750 steps; that is, 8,250 versus 6,500 ± 3,300 steps/day for the intervention group over the control respectively (power = 0.90; alpha = 0.05). Our sample size estimate for our primary outcome is also sufficiently powered to detect a clinically meaningful difference between the groups of 0.5% for HbA1c assuming a baseline HbA1c of 7.2 ± 1.2%. This baseline estimation of HbA1c was derived from data provided by the Alberta Diabetes Surveillance System [17]. Given the length of follow-up period, we conservatively estimate that the rate of attrition during the intervention could reach 20% [51], and so our sample size was increased to 110 per group to account for the possibility of loss to follow-up.

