**Method:**

Using a non-randomized design, participants (total N = 110 per group) will be consecutively allocated in bi-monthly blocks to either a 6-month self-management program lead by an Exercise Specialist or to usual care. Our primary outcome is self-reported physical activity and pedometer steps.

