#### Patient allocation

Patients will be allocated to a control group (i.e., usual care) or the intervention group using an “On-Off” group assignment method (Figure 1) This method has been previously used in quality improvement studies [19-21], and meets study design quality criteria to permit inclusion in the Cochrane Collaborations’ Effective Practice and Organization of Care (EPOC) systematic reviews [22]. Conceptually, eligible PCN patients will enter a “recruitment pool” then allocated to the intervention or control group in sequential clusters. This recruitment cluster will be filled through a number of strategies, with an aim of 50 participants at a time. The first strategy will be through active identification of newly diagnosed patients on each of the PCN’s diabetes patient registry. It is recognized that not all newly diagnosed patients will be immediately identified through this registry and therefore as a second strategy, we will recruit newly diagnosed patients through other PCN referral registries (i.e., patients attending basic diabetes education classes). Newly diagnosed patients will be given priority entry into the intervention since they may be more likely to adopt new behaviours versus those having diabetes for a longer period of time.

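### The secondary biomarker models leave out baseline drug treatment, which the trial collects and which non-randomised allocation does not balance

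*Protocol article*

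**What the plan says.** The design is non-randomised: "Using a non-randomized design, participants (total N = 110 per group) will be consecutively allocated in bi-monthly blocks" (Abstract, Method). Under Patient allocation, each recruitment pool is filled first with newly diagnosed patients: "Newly diagnosed patients will be given priority entry into the intervention since they may be more likely to adopt new behaviours". If a two-month block does not fill, the remaining places go to patients drawn at random from an earlier mail-out to everyone with diabetes on the registry.

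Biomarkers are secondary: "Secondary outcomes include nutrition behaviours (healthy eating and glycemic index), anthropometric assessments, and biomarkers" (Study measures). The Clinical measures section lists instruments to "assess hemoglobin A1c (DCA Vantage), lipid profile, glucose (Cholestech LDX), resting heart rate and blood pressure (BPTru", used at baseline, 3 and 6 months. The sample-size text gives HbA1c its own target, a 0.5-point difference with a baseline of 7.2 and SD 1.2, and calls the study sufficiently powered for it.

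Medication use is collected. The Other measures section includes "problem areas in diabetes [39], medication use, foot care, smoking behaviour", and Study measures says that health and medical characteristics are assessed at all three visits.

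The Analytic strategy uses the baseline value of each outcome as a covariate and then adds: "Potential confounding variables (i.e., age, sex and BMI) will be included as covariates in the models". Medication is not named in the models, and no text says that drug treatment is held stable during follow-up.

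**The concern.** Glucose-lowering, lipid-lowering and blood-pressure drugs act directly on the biomarkers being compared. In a randomised trial their baseline use would balance on average. Here the arms are filled block by block, and the share of newly diagnosed patients can change from one block to the next. Treatment stage plausibly follows time since diagnosis, and age, sex and BMI do not measure it.

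Adjusting for the baseline biomarker removes part of any such imbalance, but not all. Two patients with HbA1c 7.2, one on recently started treatment and one on long-stable treatment, can have different expected 6-month values with no program effect.

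At stake is the reading of the secondary clinical results. An HbA1c contrast could partly reflect a drug difference, or a real program effect could be partly hidden. The discussion section says the study will inform clinical effectiveness, so these contrasts will be read.

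**Working it through.** **Plan's own figures.** The sample-size figures are not in dispute.
- f = 0.25 corresponds to a standardised difference of 0.5. A two-sided t test at 0.05 with power 0.90 needs 86 per group, as stated.
- For steps, 1,750 with SD 3,300 gives 75 per group, as stated.
- 86 / 0.8 = 107.5, so 108, against the stated 110.

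**HbA1c precision.** The plan gives no power figure for HbA1c.
- Completers per arm after 20% attrition: 110 × 0.8 = 88.
- Unadjusted SE of the arm difference: 1.2 × √(2/88) = 0.181. Power for 0.5: Φ(0.5/0.181 − 1.96) ≈ 0.79.
- With baseline adjustment at an assumed correlation of 0.5 (the plan uses 0.5 for its primary outcome and gives none for HbA1c): SE = 1.2 × √(1 − 0.25) × √(2/88) = 0.157. Power ≈ 0.89.

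**Illustrative shift.** The documents give no drug-effect size and no expected imbalance, so both inputs are assumptions:
- residual effect *e* of a recent start or step-up on 6-month HbA1c, beyond what baseline HbA1c already reflects: 0.5 to 1.0 points;
- difference *p* between arms in the share of such patients: 10 to 20 percentage points.

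Shift = *e* × *p*; fraction of target = shift / 0.5. The last column is the probability of a two-sided significant result with no program effect: 1 − Φ(1.96 − shift/0.157) + Φ(−1.96 − shift/0.157).

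| *e* | *p* | Shift | Share of 0.5 target | Chance of a significant result |
|---|---|---|---|---|
| 0.5 | 0.10 | 0.05 | 10% | 6.2% |
| 0.5 | 0.20 | 0.10 | 20% | 9.8% |
| 1.0 | 0.10 | 0.10 | 20% | 9.8% |
| 1.0 | 0.20 | 0.20 | 40% | 24.8% |

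The nominal rate is 5%. The sign depends on which arm has more such patients. If baseline HbA1c already carries much of the drug effect, *e* and the shift are smaller. No similar calculation was made for glucose, lipids or blood pressure, because the plan gives no target differences for them.

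**The case against.** **The covariate list may not be closed.** The article uses *i.e.* loosely elsewhere: the bread swap in the intervention section is plainly an example. If age, sex and BMI are examples too, outcome-specific covariates could sit in a fuller plan. This has some force. Still, the sentence as printed states one set for all models, and it omits a collected variable with a direct effect on these outcomes.

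**The plan already offers some protection.** Baseline-value adjustment removes part of the imbalance. The planned baseline comparisons by ANOVA and chi-square could cover medication, although the variables are not listed. Both arms also run within the same networks. These points reduce the likely bias. They do not remove it, and a baseline comparison shows an imbalance without correcting for it.

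**The design limits are conceded.** The discussion calls the design weaker than a randomised trial and usual care vague. That general caveat does not mention medication and makes no use of the medication data.

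**Stronger readings that the documents do not support:**
- *Drug changes during follow-up confound the comparison.* Under the intention-to-treat approach, later changes are part of the contrast and may themselves follow from the program. An analysis limited to patients without a drug change would be selected after baseline.
- *Physicians are shown to change drugs in both arms.* The Usual care section covers the control group only, who "will receive usual or standard care for diabetes from their family physicians and/or chronic disease management team based on clinical practice guidelines", and it does not mention drugs. Ongoing medical care in the intervention arm is a reasonable inference, not a statement.
- *Newly diagnosed patients are steered to the intervention arm.* The priority-entry sentence can be read so, but the same section describes a common pool allocated in sequence. The point here needs only that the mix can vary by block.
- *The HbA1c contrast cannot be attributed to the program at all.* A partial shift of unknown direction, sized on assumed inputs, does not support that.

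**Conclusion.** The point holds for the secondary biomarkers only. Their models adjust for the outcome's baseline value, age, sex and BMI, and omit baseline drug treatment, which the trial collects and which allocation does not balance. The result is possible partial confounding in either direction. For HbA1c the illustration gives 0.05 to 0.20 points, or 10% to 40% of the 0.5-point target. It raises the chance of a significant result with no program effect from 5% to about 6% to 25%.

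Those figures rest on the assumed drug effect and imbalance, 88 completers per arm, SD 1.2 and a baseline correlation of 0.5. They show what is plausible and do not estimate the actual bias. They support saying that the contrast cannot be confidently attributed to the program, and no more. The primary outcome, physical activity by self-report and pedometer, is untouched.

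**What to change.** In the Analytic strategy, make the covariates outcome-specific for the biomarkers:
- HbA1c and glucose: add baseline glucose-lowering treatment.
- Lipids: add baseline lipid-lowering use.
- Blood pressure: add baseline antihypertensive use.

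Report medication use by arm at baseline and, where recorded, at 3 and 6 months. Collection at the later visits is inferred from Study measures, because the Other measures section does not date it. Keep the all-participants intention-to-treat model as the main analysis, describe it as the effect regardless of later drug changes, and do not adjust for drug changes after allocation.

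The cost is one or two extra terms per model and some coding of medication data; no new visits or participants are needed. The gain is also limited. The documents do not show that drug class, dose or recency of starting is recorded. Baseline use may capture treatment stage only in part, and residual confounding should be acknowledged when these results are reported.

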**Figure 1 F1:**
[figure not shown]
Study flow diagram.

Cut-point dates will be set to stop filling the recruitment pool over a two-month time frame (i.e., bi-monthly block). If the recruitment cluster fails to fill with newly diagnosed patients (i.e., less than 50 eligible), a third strategy for recruitment will be implemented which will have the remaining program invitation spots randomly selected from a second pool of patients who were contacted through an earlier pre-screen mail out to all diabetic patients on the PCN patient registry.

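### Baseline stage of change is measured in both arms but is not a model covariate, so residual confounding by readiness to change may remain in the MVPA and step contrasts

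*Protocol article*

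**What the plan says.** **Allocation.** The abstract describes the design: "Using a non-randomized design, participants (total N = 110 per group) will be consecutively allocated in bi-monthly blocks". The Patient allocation section says that eligible patients enter a common pool and are "then allocated to the intervention or control group in sequential clusters". The same section states a preference and its reason: "Newly diagnosed patients will be given priority entry into the intervention since they may be more likely to adopt new behaviours".

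**Measurement.** Under Other measures, the theory-based activity variables are listed, "and stages of change will also be examined at baseline, 3 and 6 months using validated measures". The Usual care section says that the Off group undergoes the same assessments as the intervention group, so a baseline stage value should exist in both arms.

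**Role of stage.** Under Physical activity behaviours, the stage measure "will serve as a secondary behavioral outcome (to assess stage transition"). No covariate role is stated for it anywhere.

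**Adjustment.** The Analytic strategy section enters the baseline value of each outcome as a covariate in its own model. It then adds: "Potential confounding variables (i.e., age, sex and BMI) will be included as covariates in the models". Baseline stage therefore enters the model for stage but not the models for MVPA or steps.

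**The concern.** Without randomisation, the covariates in the model are the main protection against arms that differ at entry. A variable related to both arm and outcome confounds the comparison unless it is adjusted for. The protocol itself suggests one. It ties priority for the intervention to the likelihood of adopting new behaviours, and the primary outcomes (self-reported MVPA and pedometer steps) measure that kind of adoption.

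Age, sex and BMI are weak stand-ins for readiness. Baseline activity is better but incomplete: two inactive patients, one preparing to start and one not considering it, have the same baseline MVPA and can be expected to change differently. Any imbalance in that residual readiness would be counted as an effect of the program. A direct baseline measure is already being collected and is not used for this purpose.

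**Working it through.** **1. Passages set side by side**

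| Question | Protocol text | Reading |
|---|---|---|
| Is readiness linked to arm? | Patient allocation: priority rule and its stated reason | Yes, as written |
| Is readiness linked to outcome? | Same sentence; the primary outcome is activity behaviour | Yes, by the authors' own reasoning |
| Is a proxy measured at baseline in both arms? | Other measures; Usual care | Yes |
| Is the proxy in the primary models? | Analytic strategy | Not named |

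**2. The plan's own figures (Analytic strategy).** These reproduce and are not in dispute.
- f = 0.25 for two groups is d = 0.5. At two-sided alpha 0.05 and power 0.90, n = 85 per group by the normal formula and 86 by the t distribution; the plan says 86.
- Steps: 2 × (1.960 + 1.282)² × (3,300 / 1,750)² = 74.7, so 75; the plan says 75.
- Attrition: 86 / 0.80 = 107.5, so 108; the plan says 110.

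**3. Illustrative size of the bias.** The SD of 3,300 and the target of 1,750 steps/day come from the plan. The other inputs are assumptions that are not in the documents: the arms differ by 10 to 20 percentage points in the share ready to act, and ready patients change 0.25 to 0.50 SD more by 6 months at the same baseline activity.

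Bias = (difference in share) × (difference in change)
- Low: 0.10 × 0.25 = 0.025 SD; × 3,300 = 82.5, about 83 steps/day; 82.5 / 1,750 = 5%.
- High: 0.20 × 0.50 = 0.10 SD; × 3,300 = 330 steps/day; 330 / 1,750 = 19%.
- No imbalance: 0.

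**4. A second set of assumptions.** Let D be the imbalance in readiness left after adjusting for baseline activity (0.1 to 0.5 SD), and b the slope of the outcome on readiness given baseline (0.1 to 0.3 SD per SD). Bias = D × b.
- Low: 0.1 × 0.1 = 0.01 SD = 33 steps/day (2% of target).
- High: 0.5 × 0.3 = 0.15 SD = 495 steps/day (28% of target).

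**5. Effect on the test.** With 86 per group and baseline correlation 0.5 (the plan's value), and ignoring any clustering by block or site, SE = √(1 − 0.5²) × √(2/86) = 0.866 × 0.1525 = 0.132 SD. If the program has no effect, the two-sided rejection rate is [1 − Φ(1.96 − bias/SE)] + Φ(−1.96 − bias/SE).
- Bias 0.025 SD: 0.054.
- Bias 0.10 SD: 0.118.
- Range in step 4: 0.051 to 0.206.

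**6. Precision.** If stage explains a further 5% to 10% of residual variance (also an assumption), the effective sample size is multiplied by 1/(1 − 0.05) = 1.05 to 1/(1 − 0.10) = 1.11.

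**The case against.** **Patients may not know their arm when they join.** A reader might infer that On participants volunteer for a walking program while Off participants volunteer for measurement only, so that motivated people select themselves into the intervention. The documents do not support this. Recruitment is described as one path for everyone (letter, telephone prescreen, study package), with allocation from the pool afterwards. The timing of consent relative to knowledge of arm is not given. Nor does the backfill rule help that reading: "remaining program invitation spots randomly selected from a second pool of patients" describes random selection by the study, not choice by patients. This objection stands. Self-selection by arm is a possibility, and the documented route is the priority rule.

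**The priority rule may be loosely worded.** It sits among sentences on filling a recruitment cluster and may have been meant for both On and Off clusters. If so, it need not separate the arms. As written, however, it refers to entry into the intervention.

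**The covariate list may not be exhaustive.** The article sometimes uses i.e. where it means for example, as in the bread exchange in the nutrition paragraph, and a fuller list may exist elsewhere. This weakens any claim that readiness was deliberately excluded. Still, the three named variables are the only ones given besides baseline outcome, and stage is assigned a different role.

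**Baseline activity already does much of the work.** The stage measure concerns activity of at least moderate level, the same behaviour as MVPA, so overlap is likely. This stands: only readiness that remains imbalanced after that adjustment can bias the result.

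**Psychological scores may be contaminated.** If some patients know their arm before the baseline questionnaire, intention and self-efficacy could already reflect the prospect of a program, and adjusting for them could remove part of the effect. This is why those scores belong in a sensitivity analysis.

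**The limitation is acknowledged.** The discussion concedes that the design is weaker than a randomised trial. That is candid, but it does not make use of the available covariate.

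**Conclusion.** The point holds in a limited form. The protocol links likelihood of behaviour change to priority for the intervention, measures a direct proxy at baseline in both arms, and does not name that proxy as a covariate in the MVPA and step models. Residual confounding by readiness may therefore remain.

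Neither size nor direction can be derived from the documents. The range of 83 to 330 steps/day depends on assumed imbalance and assumed differential change, and the wider range of 33 to 495 on other assumed values. A reader might infer that the bias favours the program. The priority rule makes that plausible, but no figure in the protocol establishes it. At the upper end the bias would matter for interpretation; at the lower end it is negligible. The case for acting rests on the low cost and on fixing the choice before the outcome data are seen.

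**What to change.** In the Analytic strategy section:
- Add baseline stage of physical activity change to the prespecified covariates of the primary 6-month MVPA and step models, as one ordinal term. Use the baseline value only, because later values are outcomes.
- State that this model gives the primary estimate.
- Report two sensitivity analyses: the model without stage, and a model that also includes baseline activity intention or self-efficacy.
- State how missing baseline questionnaire scores will be handled.

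The measures are already scheduled in both arms, so no new data collection is needed. The cost is one or a few degrees of freedom, the missing-data rule and two extra model runs. The sample size does not change.
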